**Methods:**

Patients with hepatolithiasis eligible for left-sided hepatectomy will be recruited. The experimental design will produce two randomized arms (laparoscopic and open hepatectomy) at a 1:1 ratio and a prospective registry. All patients will undergo surgery in the setting of an enhanced recovery after surgery (ERAS) programme. The prospective registry will be based on patients who cannot be randomized because of the explicit treatment preference of the patient or surgeon or because of ineligibility (not meeting the inclusion and exclusion criteria) for randomization in this trial. The primary outcome is the LOS. The secondary outcomes are percentage readmission, morbidity, mortality, hospital costs, long-term incidence of incisional hernias, residual stone rate, and recurrence of calculus. It will be assumed that, in patients undergoing LLH, the length of hospital stay will be reduced by 1 day. A sample size of 86 patients in each randomization arm has been calculated as sufficient to detect a 1-day reduction in LOS [90% power and *α* = 0.05 (two-tailed)]. The trial is a randomized controlled trial that will provide evidence for the merits of laparoscopic surgery in patients undergoing liver resection within an ERAS programme.

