#### Conversion from LLH to OLH

Any incision used for reasons other than trocar placement or specimen extraction will be defined as a conversion. Patients allocated to LLH but converted to OLH will still be analysed in the LLH group, according to intention-to-treat principles.

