### Secondary endpoints

The secondary outcomes are biliary leak [19], haemorrhage [20], posthepatectomy liver failure [21], wound infection, intra-abdominal fluid collection or abscess, relaparotomy, mortality, long-term abdominal wall hernias, hospital costs, residual stone rate and recurrence of calculus [22]. Existent ISGLS definitions will be used to ensure the comparability and generalizability of the results. Postoperative complications will be graded based on severity according to the Clavien–Dindo definition [27] (Tables 1 and 2).

**Table 1 Tab1:** Definition of the secondary endpoints

Secondary endpoint	Definition and assessment of outcomes
Operative time	Time from beginning to end of operation
Mortality	Death due to any cause until 90 days after the operation and the reason
Morbidity	Postoperative complications will be recorded until 90 days after operation. The severity of complications will be graded according to the Clavien–Dindo classification [27]
Blood loss	Total blood loss during the operation
Intraoperative blood transfusion	Massive haemorrhage with hemoglobin level < 7 g/dl or Hct < 22
Postoperative hospital stay	Time from the day of operation until discharge(days)
Post-hepatectomy haemorrhage	Evidence of blood loss from drains and/or nasogastric tube, based on ultrasonography, as defined by ISGPS (grade A, B, or C) [20]
Biliary leak	Bilirubin concentration in the drain fluid at least three times the serum bilirubin concentration as defined as ISGLS (grade A, B or C) [19]
Post-hepatectomy liver failure	The impaired ability of the liver to maintain its synthetic, excretory, and detoxifying functions, which are characterized by an increased international normalized ratio and concomitant hyperbilirubinemia (according to the normal limits of the local laboratory) on or after postoperative day 5 as defined as ISGLS (grade A, B, or C) [21]
Intraabdominal fluid collection	Collection of fluid measuring ≥ 3 cm associated with clinical or laboratory abnormalities
Pneumonia	Presence of a new infiltrate on chest X-ray, as well as following: body temperature > 38℃, abnormal elevation of WBC, or positive sputum, and requiring antibiotic treatment
Wound infection	Surgical site infection associated with laparotomy that develops during the initial hospital stay
Abdominal rupture	Dehiscence of abnormal closure with need for resuture of the laparotomy during the initial hospital stay

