Total hospitalization expenses	Hospital costs from admission to discharge ($)
Recurrence of calculus	Calculi in the intrahepatic duct within 3 months after hepatectomy are defined as residual stones [22]

**Table 2 Tab2:** Severity grade according to the Clavien–Dindo definition [27]

Grade	Definition
I	Any deviation from the normal postoperative course without the need for pharmacological treatment or surgical, endoscopic, and radiological intervention
II	Requiring pharmacological treatment with drugs other than those allowed for grade I complications
III	Requiring surgical, endoscopic, or radiological intervention
IIIa	Intervention not under general anaesthesia
IIIb	Intervention under general anaesthesia
IV	Lifer-threatening complication. Requiring intensive care unit management
IVa	Single-organ dysfunction
IVb	Multiorgan dysfunction
V	Death of patient

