### Statistical aspects

#### Sample size calculation

The sample size calculation is based on the primary endpoint: the LOS. According to published data, an assumed 1-day reduction in LOS is the appropriate basis for the calculation, assuming 5 days in the LLH group and 6 days in the OLH group [28]. This calculation yields a total of 86 patients in each group, which assures 90% power at a two-sided level of significance of 5% [NCSS and PASS 15 (NCSS Statistical Software, Kaysville, UT, USA)]. Assuming an expected withdrawal rate of 10% during the trial, 18 additional patients will be included and randomized; therefore, the total sample size required is *n* = 190 patients (Fig. 3).

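### Table 1 counts wound infection only if it is tied to a laparotomy and arises before first discharge, which biases this secondary endpoint towards LLH and conflicts with the 90-day morbidity row

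*Protocol article*

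**What the plan says.** All places are in the protocol article.

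- **Wound infection** (Secondary endpoints, Table 1): "Surgical site infection associated with laparotomy that develops during the initial hospital stay".
- **Abdominal rupture** (same table): "Dehiscence of abnormal closure with need for resuture of the laparotomy during the initial hospital stay".
- **Morbidity** (same table): "Postoperative complications will be recorded until 90 days after operation", graded by Clavien-Dindo, with no restriction by type of incision or to the index stay.
- **Costs** (same table): "Hospital costs from admission to discharge".
- **Conversion** (Conversion from LLH to OLH): "Any incision used for reasons other than trocar placement or specimen extraction will be defined as a conversion". For analysis, "Patients allocated to LLH but converted to OLH will still be analysed in the LLH group, according to intention-to-treat principles".
- **Expected stay** (Sample size calculation): "assuming 5 days in the LLH group and 6 days in the OLH group". Length of stay is the primary outcome.
- **Readmission**: the abstract says "The secondary outcomes are percentage readmission, morbidity, mortality, hospital costs", followed by further items. The outcome list under Secondary endpoints and Table 1 do not contain readmission. Quality and safety does require it to be reported as a serious adverse event.

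**The concern.** A safety endpoint should give a patient the same chance of being counted in either arm if the true risk is the same. The wound-infection row departs from this in two ways.

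1. **Which wounds count.** Almost every OLH patient has a laparotomy. An LLH patient has one only after conversion, unless an extraction incision is taken to be a laparotomy, which the article does not say. The randomized treatment therefore largely decides whether an infected wound can enter the numerator.
2. **How long patients are watched.** Counting stops at first discharge. The trial expects LLH to bring discharge forward, so the arm that does better on the primary outcome is observed for less time on this one.

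If the row is applied as written, the report could show fewer wound infections after LLH when none were prevented. The same patients would also appear differently in the morbidity row, and the two results could not be reconciled. Abdominal rupture has the same window and is likewise limited to the laparotomy.

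**Working it through.** **The plan's own figure.** No figure is stated for wound infection, rupture or costs. The only relevant number is 86 per group. The article gives no SD. With an assumed SD of 2.0 days,

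n = 2 × (1.960 + 1.282)² × 2.0² / 1² = 84.06, so 85 per group, or 86 with the t distribution.

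Solving back from 86, SD = √(86/2) / (1.960 + 1.282) = 2.02. The figure is thus reproduced conditionally on that SD. Nothing below depends on the SD; 86 is used only as the arm size.

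**Step 1: laparotomy condition alone.** Let p be the true in-hospital infection risk, equal in both arms, and c the conversion rate. OLH counts p; LLH, read literally, counts c × p. Both p and c are assumptions. With c = 10% and 86 per arm:

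| True risk, both arms | OLH counted | LLH counted | Fisher P < 0.05 | Same, if all incisions counted |
|---|---|---|---|---|
| 5% | 5% | 0.5% | 19% of trials | 2% |
| 10% | 10% | 1.0% | 67% | 3% |
| 15% | 15% | 1.5% | 90% | 3% |

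At p = 10%, a normal approximation gives 86% with no conversions, falling to 60% with 20% conversions. It runs above the exact test (74% against 67% at 10% conversion).

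**Step 2: window alone.** Take stays of exactly 5 and 6 days and equal risk, with all incisions counted.

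- Onset uniform over 30 days (assumed): 5/30 = 0.167 and 6/30 = 0.200; ratio 0.83. A constant hazard gives almost the same.
- Onset lognormal, median 9 days, sigma 0.5 (assumed): F(5) = 0.120 and F(6) = 0.209; ratio 0.57.
- Lognormal medians of 5 to 12 days with sigma 0.4 or 0.6: ratios from 0.34 to 0.81.

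With a 30-day risk of 5-15% and uniform onset, so few events are counted that Fisher's test is falsely significant in under 1% of trials.

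**Step 3: both conditions, with p as a 30-day total.** With uniform onset and 10% conversion, OLH counts p × 6/30, which is 1.0%, 2.0% or 3.0%. LLH counts 0.10 × p × 5/30, which is 0.08%, 0.17% or 0.25%. The ratio is 0.10 × 5/6 = 0.08. False significance stays under 4%, but the estimate is still heavily distorted.

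**Step 4: the rows of Table 1 side by side.** A port-site infection on day 10, after discharge on day 5, counts as morbidity. It fails both conditions of the wound-infection row. An infected open incision on day 10, after discharge on day 6, also counts as morbidity but not as wound infection. The rows disagree in both arms; the laparotomy condition makes the disagreement unequal.

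**Step 5: costs.** Stopping at discharge omits readmission costs in both arms. The sign of any bias depends on which arm has more post-discharge cost, and the article gives no readmission rate or cost by arm. It cannot be computed.

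**The case against.** The strongest reply is that the row is loosely worded rather than a settled rule. The outcome list simply names wound infection. The Blinding section foresees suspected wound infection under a dressing that covers the incision or incisions of patients in either arm. The conversion rule says an extraction incision is not a conversion; it does not say that it is not a laparotomy. This stands as far as it goes: a count of zero in unconverted LLH patients follows only from the literal reading. But Table 1 is where the endpoint is defined, and nothing in the article supplies a broader definition.

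A reader might also infer that events after discharge would be invisible. The documents do not support that. The morbidity row runs to 90 days, contacts take place at 1 and 3 months, and readmission is reported as a serious adverse event.

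For abdominal rupture, having no laparotomy that can dehisce is partly a genuine benefit of the laparoscopic approach. What the row wrongly misses is dehiscence at trocar and extraction sites, and dehiscence after discharge.

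Finally, the sizes rest on assumed risks, conversion rates and onset distributions, and on fixed stays that ignore the spread in LOS. This stands too: the direction comes from the definition, the size from the assumptions. The window fault also depends on LLH stay actually being shorter.

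**Conclusion.** The concern holds for wound infection as a named secondary endpoint. As written, the definition depends on the arm, ends observation at the primary outcome, and conflicts with the 90-day morbidity row. It holds in part for abdominal rupture.

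The laparotomy condition is the larger fault. If 5-15% is the in-hospital risk in both arms and 10% of LLH patients are converted, LLH records a tenth of the true events, and a test at 86 per arm is falsely significant in 19-90% of trials. If the same risk is a 30-day total with uniform onset, false significance falls below 4% while the bias in the estimate remains. The window alone biases the ratio, to about 0.83 with uniform onset, but rarely produces a significant result.

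Two stronger readings should be resisted. One is that the safety comparison as a whole is biased towards LLH: LOS, its sample size and overall 90-day morbidity are untouched. The other is that the cost endpoint favours LLH by definition: the same window applies to both arms, and the direction of any bias cannot be determined from the documents. The readmission mismatch is an inconsistency in the endpoint list and does not itself show bias.

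**What to change.** 1. In Table 1, define wound infection as infection of any operative incision (laparotomy, trocar or extraction site), and abdominal rupture as dehiscence at any of these. Use one fixed window from surgery in both arms, regardless of discharge. The protocol's own 90 days is the natural choice.
2. Report in-hospital events separately beside the fixed-window result.
3. Reconcile readmission between the abstract, which lists it, and the Secondary endpoints section, which does not. If it is kept, state its window; the article gives none.
4. Either label costs as index-stay costs, or add readmission costs over a fixed period.

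**Cost.** Items 1 to 3 are mainly changes of wording, because complications are already recorded to 90 days and readmissions are already reported. Adding readmission costs would require further billing data; relabelling would not.

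There are two modest drawbacks. Follow-up may be by telephone and patients learn their allocation after POD3, so post-discharge wound events rest partly on unblinded reports. Recruitment began in August 2019, so the definition would change during the trial; the change should be dated and made before outcome data are compared by arm. Item 2 lets readers see whether either matters.

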### Data collection and patient follow-up

Data will be collected prospectively for all patients, including history, physical examination, laboratory data, pathologic examination, perioperative clinical information, and complications. Data will be collected via datasheets on paper and kept securely. Study subjects will complete the examinations at inclusion, 1 week after surgery, and 3, 6, 12, 24, and 36 months postoperatively. Follow-up will be conducted at 1 month postoperatively and then 3, 6, 12, 24, and 36 months postoperatively by telephone or as outpatients with liver function tests and abdominal ultrasonography for 3 years or until death. CT or MRCP will be performed in cases of suspected stone recurrence or cholangitis (Table 1). All handling cases will be managed by subject identification codes or anonymized registration numbers. The correspondence table of the anonymizing code and names and the consent form containing the names will be kept strictly in separate lockable document storage. All required parameters will be collected in an SPSS data file (SPSS version 25, IBM statistics, Chicago, IL, USA).

### Definitions

Functional recovery is reached when all of the following criteria are met: adequate pain control with only oral analgesia, restoration of mobility to a level of independence, ability to maintain sufficient caloric intake (a minimum of 50% of the required daily intake), no need for intravenous fluid administration, and no signs of active infection (fever or other clinical symptoms) [15]. Complications will be classified using the Clavien–Dindo score [27]. Major complications will be defined as a Clavien–Dindo grade III or higher.

### Quality and safety

The surgical experience of surgeons can affect complication rates, which might bias the results. To prevent surgeon bias, surgeons should meet the following criteria: (1) have performed more than 200 open hepatectomies, (2) have performed more than 100 laparoscopic hepatectomies, and (3) be qualified surgeons according to the China College of Laparoscopic Hepatectomy. LLH will be performed by two surgeons ([name] and [name]), and OLH will be performed by four surgeons ([name], [name], [name], and [name]).

Serious adverse events that have to be reported to the study coordinator within 24 h include unplanned intensive care unit admission; any surgical, endoscopic, or interventional radiology intervention (excluding feeding tube placement); readmission; and mortality (regardless of cause).

### Statistical aspects

#### Sample size calculation

The sample size calculation is based on the primary endpoint: the LOS. According to published data, an assumed 1-day reduction in LOS is the appropriate basis for the calculation, assuming 5 days in the LLH group and 6 days in the OLH group [28]. This calculation yields a total of 86 patients in each group, which assures 90% power at a two-sided level of significance of 5% [NCSS and PASS 15 (NCSS Statistical Software, Kaysville, UT, USA)]. Assuming an expected withdrawal rate of 10% during the trial, 18 additional patients will be included and randomized; therefore, the total sample size required is *n* = 190 patients (Fig. 3).

**Fig. 3 Fig3:**
[figure not shown]
Flow chart according to CONSORT. X means there is no fixed number and that patients would recruit until the randomized element is full

#### Statistical analysis

The two-sided null hypothesis for the primary endpoint states that both study interventions will lead to a similar time to the LOS; the alternative hypothesis is that one intervention will perform better than the other. The null hypothesis will be tested by analysing the covariance while adjusting for age and the type of liver resection. A binary logistic regression will be applied to compare the time to functional recovery between groups after adjusting for other factors. Background characteristics and surgical outcome measures will be compared using chi-squared or Fisher’s exact tests for categorical data and two-tailed* t* tests or nonparametric Mann–Whitney *U* tests for continuous variables. Categorical data will be presented as the frequencies and group percentages, and continuous variables will be expressed as the means and standard deviations. The homogeneity of the two groups will be described by comparison of the demographic data and baseline values. All analyses will be performed on an ITT basis [17]. For the ITT analyses, the data will be processed for all trial patients in their randomized groups. A *P* value < 0.05 will be considered statistically significant. All statistical calculations will be performed using SPSS 22.0 (SPSS version 25, IBM statistics, Chicago, IL, USA).

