### Randomization

Patient recruitment and the collection of written informed consent will be performed at the outpatient clinic. Patients will be randomized to the different groups using the block randomization method. Each block contains two groups: the OLH group and the LLH group. The block size will be hidden from the trial executors and clinicians. Possible balanced combinations of these groups within the block will be numbered consecutively. Then, blocks will be randomly chosen using the ‘randomize’ library of SPSS 22.0 (SPSS, Chicago, USA), and a series of randomly assigned OLHs and LLHs will be generated based on the random sequence of blocks. Allocation will be concealed using sequentially numbered, sealed opaque envelopes prepared by a member of our Clinical Trial Center. Patients will be randomly allocated to either OLH or LLH before surgery. The trial executors will receive randomly generated treatment allocations within sealed opaque envelopes. Afterwards, medical staff will personally inform the expert surgeon as to which treatment group the patient has been randomized. To avoid any potential prediction of group allocation, information on the block length will be kept away from the study site.

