### Primary endpoint

The primary outcome of this trial is the LOS. Only the researchers and surgical surgeons will know the true operation. A blinded ward doctor will decide whether the patient should be discharged.

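### The primary ANCOVA on LOS is valid, but adding ASA class, which must be established at entry, would gain a little precision at almost no cost

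*Protocol article*

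**What the plan says.** The Primary endpoint section states: "The primary outcome of this trial is the LOS". The Statistical analysis section gives the primary test in one sentence: "The null hypothesis will be tested by analysing the covariance while adjusting for age and the type of liver resection". That names two covariates and defers no others.

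ASA class appears among the inclusion criteria, which admit classes I to III. The Randomization section says "Patients will be randomized to the different groups using the block randomization method" and names no stratification factor. The Methods part of the abstract describes "two randomized arms (laparoscopic and open hepatectomy) at a 1:1 ratio".

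The Sample size calculation section plans for a one-day difference, "assuming 5 days in the LLH group and 6 days in the OLH group", and reports: "This calculation yields a total of 86 patients in each group", "which assures 90% power at a two-sided level of significance of 5" per cent. It states no SD. The Statistical analysis section also says that the groups will be compared descriptively on demographic and baseline values.

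**The concern.** ASA class is a preoperative grade of fitness and precedes allocation. It could plausibly predict days to discharge: the Background ties medical readiness for discharge to functional recovery, including mobility at the preoperative level. A prognostic baseline variable left out of the model leaves its share of the variation in the residual and widens the interval for the LOS difference. As no stratification on ASA is described, the arms may also differ in ASA mix by chance, and the planned model would not correct the estimate for that.

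The plan already uses covariance adjustment, so including ASA needs no new method. What is at stake is a modest amount of precision, not the validity of the comparison.

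**Working it through.** **Inputs from the protocol article.** Difference 1 day (6 minus 5), 86 per arm, 1:1 allocation, 90% power, two-sided alpha 0.05.

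**Inputs not in the article, assumed here.**
- SD of LOS, back-calculated below.
- R², the share of the LOS variance remaining after age and resection type that ASA explains: 1% to 10%.
- For the imbalance illustration, 25% of patients in ASA III and one extra day of stay for them.

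**Step 1: the plan's own figure.** By the normal approximation, n per arm = 2 × SD² × (1.960 + 1.282)² / 1². Setting n = 86 gives SD = 2.02. With the noncentral t distribution, SD = 2.0 needs 86 per arm and gives power 90.3%. So 86 reproduces with an SD of about 2.0 days. I treat this as the residual SD under the planned model. If age and resection type already bring the residual SD below 2.0, power starts higher and the gain from ASA is smaller.

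**Step 2: gain from adding ASA.** Residual SD = SD × √(1 − R²). Power is by noncentral t at 86 per arm for a 1-day difference. Equivalent n per arm = 86 / (1 − R²).

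| R² from ASA | Residual SD (from 2.0) | Power, SD 2.0 | Power, SD 2.5 | Equivalent n per arm |
|---|---|---|---|---|
| 0 | 2.000 | 90.3% | 74.2% | 86.0 |
| 1% | 1.990 | 90.6% | 74.6% | 86.9 |
| 5% | 1.949 | 91.7% | 76.3% | 90.5 |
| 10% | 1.897 | 93.0% | 78.5% | 95.6 |

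The gain at SD 2.0 is therefore 0.3 to 2.7 percentage points.

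**Step 3: cost if ASA is uninformative.** A three-level factor uses 2 degrees of freedom. The residual falls from 172 − 4 = 168 to 166. Power goes from 90.319% to 90.315%, which is no practical change.

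**Step 4: chance imbalance.** With 25% ASA III, the standard error of the between-arm difference in the ASA III proportion is √(2 × 0.25 × 0.75 / 86) = 0.066. One trial in 20 has an absolute difference above 1.96 × 0.066 = 0.129, or about 13 percentage points. With one extra day of stay, the shift in the LOS difference is 0.129 × 1 = 0.13 day.

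This agrees with Step 2: the implied R² is 1² × 0.25 × 0.75 / 2.0² = 4.7%, and power with ASA in the model is then 91.6%. For comparison, the standard error of the treatment difference is 2.0 × √(2/86) = 0.305 day.

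**The case against.** The strongest reply is that nothing here is wrong. The article prespecifies a valid ANCOVA with two sensible covariates. It nowhere calls ASA prognostic for LOS, stratifies on it or promises to adjust for it. Any model can be asked to take one more term, and the benefit rests on an association the document does not supply. This stands to the extent that the point is an efficiency suggestion. It does not defeat the suggestion, because the cost is close to nil even if ASA proves uninformative.

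A reader might infer that omitting ASA biases the comparison or inflates type I error. It does neither. ASA imbalance under randomisation is random, and the standard error already covers it.

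A reader might also put the imbalance effect at about a quarter of the target difference by assuming that ASA III adds two days: 0.129 × 2 = 0.26 day. That implies R² = 4 × 0.1875 / 4 = 18.75%, well outside the 1% to 10% range used for power. No figure in the document supports so strong an effect.

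Two further reservations are fair. Complete ASA data are an inference from eligibility, since the data collection section does not name ASA class. And recruitment began in August 2019, with researchers who know which operation was done, so a change to the primary model needs a documented date and rationale. The planned baseline comparison could describe an ASA imbalance but would not correct the estimate, and adding the term after seeing an imbalance would be a data-driven choice.

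**Conclusion.** The point holds as a minor efficiency improvement. At 86 per arm, adding ASA class raises power from about 90.3% to between 90.6% and 93.0%. It also reduces, without eliminating, the effect of a chance ASA imbalance, whose 1-in-20 size is about 0.13 day in the illustration. These figures depend on the back-calculated SD and on the assumed R², ASA III share and extra stay. None of these is stated in the document. If ASA adds nothing beyond age and resection type, nothing is gained and practically nothing is lost.

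The document does not support calling the planned model biased, invalid or in conflict with another section. The primary analysis can stand as written, and no conclusion of the trial should be expected to turn on this change.

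**What to change.** Amend the primary-analysis sentence in the Statistical analysis section so that LOS is tested by analysis of covariance adjusting for age, type of liver resection and ASA class, with ASA entered as a three-level factor (I, II, III). Date and record the amendment before anyone makes a comparative look at the data, and confirm that ASA class is captured on the case report form. If the sponsor prefers the present model, a sentence on why age and resection type suffice would close the point.

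The cost is one line of analysis wording, 2 degrees of freedom and a documented amendment. No extra patients or visits are needed, and no new data provided that the ASA class established at screening is recorded.

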The day of discharge from the hospital is dependent on multiple factors, including patient expectations, local discharge logistics, cultural differences between countries, hospitals, and surgeons. LOS may therefore be considered an inappropriate endpoint for comparison of surgical interventions. Within the ERAS programme for liver surgery, a composite endpoint has been defined: time to functional recovery [15]. This endpoint, representing medical readiness for discharge, consists of clear and objectively measurable criteria. A patient is considered functionally recovered if they have a normal or decreasing serum bilirubin level, good pain control with oral analgesia only, tolerance of solid food, no intravenous fluid support, and independent mobility at the preoperative level [15]. Functionally recovered patients are generally capable of performing activities of daily living independently and are independent of hospital care. Therefore, we will conduct this randomized controlled trial to evaluate the safety and effectiveness of LLH for hepatolithiasis by comparing its clinical outcomes with those of OLH.

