### Blinding

In this trial, all assessors of the primary outcome (i.e. the ward doctor), the patients, and the adjudication committee will be blinded to the operation allocation. Directly after skin closure, while still under general anaesthesia, patients will receive a firmly taped, large 40 × 40 cm abdominal dressing to cover their incision(s) and therefore their treatment allocation (minimally invasive or open). This abdominal dressing will be removed when all criteria for functional recovery are met or earlier for medical reasons, such as suspicion of wound infection. If an earlier inspection is needed, attempts will be made to maintain patient blinding.

The success of blinding will be assessed using the blinding index as proposed by Bang et al. [23]. Both patients and ward doctors will be asked about the alleged treatment allocation based on five categories: (1) strongly believe it was LLH, (2) somewhat believe it was LLH, (3) somewhat believe it was OLH, (4) strongly believe it was OLH, and (5) do not know. Sensitivity analysis will be performed for the analysis of time to functional recovery.

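### Time to functional recovery, a duration in days, is assigned a binary logistic regression with no yes/no coding stated; a supportive outcome is affected, not the primary LOS analysis

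*Protocol article*

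**What the plan says.** The Statistical analysis section gives each of two outcomes its own model. For the primary endpoint: "The null hypothesis will be tested by analysing the covariance while adjusting for age and the type of liver resection". For functional recovery: "A binary logistic regression will be applied to compare the time to functional recovery between groups after adjusting for other factors".

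Three other places describe functional recovery:

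- Background: "Within the ERAS programme for liver surgery, a composite endpoint has been defined: time to functional recovery". The same paragraph argues that discharge depends on non-medical factors and presents this endpoint as an objective measure of readiness to leave hospital.
- Definitions: "Functional recovery is reached when all of the following criteria are met: adequate pain control with only oral analgesia", followed by four further conditions. The event occurs when the last condition is met.
- Blinding: "Sensitivity analysis will be performed for the analysis of time to functional recovery".

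Its standing is also clear. Under Primary endpoint: "The primary outcome of this trial is the LOS". Time to functional recovery does not appear in the Secondary endpoints section, in Table 1 or among the outcomes in the abstract.

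**The concern.** The outcome is a number of days and the model is for a two-level response. To run the sentence as it stands, the analyst must first make a coding decision that the article does not state, and that decision determines what is being compared.

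If patients are coded as ever recovered or not, nearly all will be events and little is left to compare. If they are coded as recovered by some day, the timing on either side of that day is lost and the answer can change with the day chosen. Meanwhile the label on the result would still say that times were compared.

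The stake is moderate. The Background puts this outcome forward because LOS can be swayed by logistics and expectations, so readers will look at it when they interpret LOS. It is also the only outcome to which the article attaches a blinding-related sensitivity analysis.

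**Working it through.** **Step 1. Method against outcome.** Background, Definitions and Blinding all treat the outcome as a time, or as an event that falls on a day. Only the sentence in Statistical analysis implies a binary response. No section supplies a link between the two: there is no reference day, no outcome of the form 'recovered by day X', and no mention of person-day records. The mismatch therefore stands on the text alone.

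**Step 2. Planning values.** The article gives none for functional recovery, so the LOS values are borrowed as an illustration.

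- Means: "assuming 5 days in the LLH group and 6 days in the OLH group" (Sample size calculation).
- Size: 86 per arm, 90% power, two-sided 5% (same section).
- SD: not stated. Solving the normal formula for it gives √(86/2) / (1.960 + 1.282) = 6.557 / 3.242 = 2.02 days, so SD = 2 is assumed.

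Check: n = 2 × 2² × (1.960 + 1.282)² / 1² = 84.06, which rounds up to 85. The t-test version gives 85.03, rounded up to 86, with power 0.903 at 86. The article's 86 is reproduced under that SD.

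**Step 3. 'Recovered by day c'.** With p₁ and p₂ the proportions recovered by day c and p̄ their mean:

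power = Φ[(|p₁ − p₂| − 1.96·SE₀) / SE₁], where SE₀ = √(2p̄(1 − p̄)/86) and SE₁ = √((p₁(1 − p₁) + p₂(1 − p₂))/86).

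Example, normal times, c = 5.5: p₁ = 0.599, p₂ = 0.401, SE₀ = 0.0762, SE₁ = 0.0747. Then (0.1974 − 0.1494)/0.0747 = 0.64, and Φ(0.64) = 0.74.

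| Cut-off day | Normal: p₁, p₂ | Power | Lognormal: p₁, p₂ | Power |
|---|---|---|---|---|
| 3 | 0.159, 0.067 | 0.48 | 0.129, 0.024 | 0.73 |
| 4 | 0.309, 0.159 | 0.64 | 0.350, 0.139 | 0.90 |
| 5 | 0.500, 0.309 | 0.73 | 0.576, 0.345 | 0.87 |
| 5.5 | 0.599, 0.401 | 0.74 | 0.670, 0.458 | 0.81 |
| 6 | 0.691, 0.500 | 0.73 | 0.747, 0.564 | 0.72 |
| 7 | 0.841, 0.691 | 0.64 | 0.857, 0.738 | 0.49 |
| 8 | 0.933, 0.841 | 0.48 | 0.921, 0.853 | 0.29 |

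The lognormal columns keep means of 5 and 6 days and SD 2.

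**Step 4. 'Ever recovered'.** The article gives no recovery proportions. With assumed values of 99% against 98% the same formula gives power 0.08; with 99% against 97% it gives 0.15.

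**Step 5. Analysing the days themselves.** For times rounded to whole days, simulated power was as follows:

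- Log-rank: about 0.83 for lognormal and 0.86 for normal times.
- t-test: about 0.90 for lognormal and 0.89 for normal times (0.90 by formula).

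**The case against.** Four points can fairly be made against this.

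*Standing.* The sample size and the hypothesis test rest on LOS, and the primary test is an analysis of covariance. A reader might infer that the trial's main conclusion is at risk. The documents do not support that, because nothing in the primary analysis depends on this sentence. This stands and limits the severity.

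*Logistic regression can handle times.* Fitted to one record per patient per day, it is a recognised discrete-time hazard model. So it would be wrong to say that the method can never be used for a time. But the article describes no such set-up, and the sentence does not imply one.

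*The analysis plan may hold the detail.* Data Availability lists a statistical analysis plan that is not shown here. A cut-off day, the coding and the list of adjustment factors could be in it. A reader might infer that the cut-off will be picked after seeing the data; that is a risk the wording leaves open, not something the article shows. What remains is that the article is not silent: it names a method that does not fit the outcome as the article describes it.

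*The power loss is borrowed and not uniform.* The SD is back-calculated and, with the means, carried over from LOS, which the Background itself distinguishes from readiness for discharge. In the lognormal illustration a split at day 4 (90%) or day 5 (87%) does better than the log-rank test (83%). The tempting claim that dichotomising always costs power against a time-to-event analysis therefore fails; in the illustration it holds only for normal times. The figures show dependence on the cut-off, not a fixed loss.

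**Conclusion.** The point holds as a mismatch between method and outcome, wrong as written rather than merely brief. It affects the supportive comparison of functional recovery and the sensitivity analysis under Blinding, and it should be corrected before any unblinded analysis.

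No figure in the article is contradicted. The illustration indicates how much the missing coding matters. Over cut-offs at days 3 to 8, power ranges from 48% to 74% (normal) or 29% to 90% (lognormal), and it is 8–15% for 'ever recovered' under the assumed proportions. These numbers assume that functional recovery behaves like LOS, with a 1-day effect, SD 2 and 86 per arm. They should not be quoted as the trial's actual power for this outcome.

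**What to change.** First reconcile the two definitions of functional recovery. The Background list includes a bilirubin criterion and tolerance of solid food. The Definitions list has no bilirubin criterion, sets a minimum caloric intake and adds absence of active infection. The recovery day cannot be fixed until one list applies.

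Then replace the sentence in Statistical analysis. One workable form: *Time from surgery to functional recovery, in days, will be compared between randomized groups with a Cox model adjusted for age and planned type of resection, and shown with cumulative-incidence curves. Death before recovery will be treated as a competing event.* The text should also say whether the model is cause-specific or subdistribution, and give a rule for patients who withdraw or are discharged before meeting the criteria. The sensitivity analysis under Blinding should refer to the same model.

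A coherent alternative is to keep logistic regression, prespecify 'recovered by day X', and rename the outcome accordingly. Either way, replace the unspecified adjustment factors with a named list.

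The cost is a short text amendment. No new data are needed, provided that the day of recovery and the components of the reconciled definition are already being recorded. The Blinding section makes the first of these likely, since it ties removal of the dressing to recovery.
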